## Assessment of outcome

The primary outcome measure for this study will be the Knee Society Score [12] at 52 weeks, and will be carried out by a trained independent assessor (physiotherapist) who will be blinded to the surgical approach taken.

### Secondary outcomes – patient based

1. EuroQol-5D [10]. A simple, generic measure of health outcome. It allows an accurate self-description of current health related quality of life, assessing mobility, self-care, usual activity level, pain/discomfort and anxiety/depression.

2. WOMAC Osteoarthritis Index [11]. An osteoarthritis specific measure of health outcome, assessing pain, stiffness and activity level.

3. SF-36 [13]. A comprehensive generic measure of health outcome.

4. Time to normal activities/return to function (days/weeks)

5. Pain (7 day pain diary – visual analogue scale 0–100)

### Secondary outcomes – medical records

1. Complications (in hospital or requiring readmission during 12 month follow-up)

2. Length of stay in hospital (days)

3. Tourniquet time (minutes)

4. Blood loss (litres)

5. Post-operative use of analgesia (7 day analgesia diary recorded by nurse)

6. Surgeons ease of exposure score (VAS 0–100) – form inserted in notes

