## Background

There is general agreement about the value of knee replacement surgery, with approximately 30,000 knee replacements performed annually in the UK. However, there is uncertainty as to the best surgical approach to the knee joint.

Total knee replacements through a standard medial parapatellar arthrotomy [1] are routinely carried out. The sub-vastus (southern) arthrotomy has been suggested as an alternative [2]. There have been two previous published trials of the sub-vastus approach versus a standard medial parapatellar approach.

In the first of these [3], 20 patients undergoing bilateral knee arthroplasty were studied, with follow-up at 1, 4 and 12 weeks post-operatively. The patients whose knee was approached by the sub-vastus method showed 35% and 16% greater quadriceps strength at 1 week and 1 month respectively. In addition, the authors highlighted several anatomical advantages. The approach maintains the medial parapatellar blood supply and preserves the extensor mechanism [4-6]. Thus, theoretically, it decreases the likelihood of patellar subluxation, fracture, or patellar avascular necrosis (reported as having an incidence of 17%, 21% and 10% respectively) [7,8].

In the second of these trials [4], 41 consecutive primary knee arthroplasties were studied with follow-up at 6 months. Patients who had the sub-vastus approach were able to straight leg raise 4 days sooner (p = 0.008) and used 40% less post-operative analgesia (p = 0.05). They also spent on average 3 days less in hospital (p = 0.01).

The subvastus approach has also been reported to have decreased wound complications, a shorter hospital stay, a reduction in analgesia usage and an early return to function when compared to the standard median parapatellar approach [2,4,9].

There were problems with the validity and quality of both studies, as they were not truly randomised, and involved only a small number of patients and follow-up was short. Long term follow-up is needed to determine whether potential short term benefits increase long term effectiveness. A larger sample size will allow a wider range of outcomes to be investigated (in particular knee function) and a broader range of patients to be recruited to improve external validity and allow for sub-group analysis (e.g. by age and sex). Furthermore, involving more surgeons will allow assessment of variation in outcome by individual surgeons.

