## Assessments/data collection

All trial proformas will be supplied in a separate booklet and will form the basis of the patients case report form. Assessment will be conducted pre, peri and post-operatively. Data on the primary and all patient based and independently assessed secondary outcome measures will be collected at 1, 6, 12, and 52 weeks postoperatively. These assessments are timed to coincide with routine clinical practice.

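### Complications without readmission are counted only until discharge, so if stay differs between arms the complication comparison favours the arm with the shorter stay

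*Protocol article*

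**What the plan says.** Under "Secondary outcomes – medical records", the protocol article lists "Complications (in hospital or requiring readmission during 12 month follow-up") and, as the next item, "Length of stay in hospital (days"). An event qualifies either because it happens before discharge or because it brings the patient back into hospital within the year.

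The section Assessments/data collection sets the visit schedule: "Data on the primary and all patient based and independently assessed secondary outcome measures will be collected at 1, 6, 12, and 52 weeks" after surgery. Outcomes taken from medical records, which include complications, are not named there.

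On length of stay, the Background reports of an earlier study of 41 arthroplasties: "They also spent on average 3 days less in hospital (p = 0.01"). It adds: "The subvastus approach has also been reported to have decreased wound complications, a shorter hospital stay", among other benefits. The same section then criticises both earlier trials for their randomisation, their small size and their short follow-up.

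The section Data analysis assigns the chi-square test to categorical data and places all secondary outcomes among the principal comparisons.

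**The concern.** The rule is worded identically for both arms, but it does not guarantee them equal observation. For a complication that never needs readmission, the clock stops at discharge. If one approach sends patients home sooner, a wound problem arising on the same post-operative day could be counted in a patient still on the ward and missed in a patient already at home.

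A chi-square test compares proportions and does not allow for unequal observation time. Any resulting bias would favour the arm with the shorter stay. If earlier reports are borne out, that is the sub-vastus arm, and fewer wound complications is one of the benefits the Background attributes to that approach. A reader of the results could not separate a real reduction from a shorter period of counting.

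**Working it through.** The protocol gives no complication rate, power or sample size for this outcome, so there is no stated figure to reproduce. The check is the logic of the definition plus an illustration.

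**Inputs from the protocol article**
- Counting rule: in hospital, or requiring readmission within 12 months (Secondary outcomes – medical records).
- Gap in stay: 3 days, from one earlier study (Background).
- Patients per arm: 105 before the allowance for loss to follow-up (Sample size), used for scale only.
- Test: chi-square (Data analysis).

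**Assumed, because the protocol gives no values**
- True risk R = 20%, the same in both arms.
- Exponential onset with mean τ = 5, 10 or 20 days, so the share of events that have occurred by day L is F(L) = 1 − exp(−L/τ).
- Fraction f of post-discharge events needing readmission: 10% or 30%.
- Stays of 4 v 7, 7 v 10, 9 v 12 or 11 v 14 days, the same for every patient in an arm.

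**Formula.** The expected recorded proportion in an arm with stay L is

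P(L) = R × [F(L) + (1 − F(L)) × f].

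The difference between a longer stay L1 and a shorter stay L2 is

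P(L1) − P(L2) = R × (1 − f) × [F(L1) − F(L2)].

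This is zero if L1 = L2 or if f = 1. Otherwise it is positive, so under this model the direction does not depend on the assumed values.

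**One case in full** (7 v 10 days, τ = 10, f = 10%):
- F(7) = 1 − exp(−0.7) = 0.503, so P(7) = 0.20 × (0.503 + 0.497 × 0.1) = 11.1%.
- F(10) = 1 − exp(−1) = 0.632, so P(10) = 0.20 × (0.632 + 0.368 × 0.1) = 13.4%.
- Risk ratio 0.83, gap 2.3 percentage points, with no true difference.

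**All cases** (range over τ and f). The last column is the chance of a significant result favouring the shorter-stay arm at 105 per arm; its nominal value in that direction is 2.5%.

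| Stay (days) | Recorded risk ratio | Gap (percentage points) | Chance of false significance |
|---|---|---|---|
| 4 v 7 | 0.72 to 0.84 | 1.6 to 3.6 | 6% to 12% |
| 7 v 10 | 0.81 to 0.91 | 1.4 to 2.3 | 5% to 7% |
| 9 v 12 | 0.84 to 0.94 | 1.0 to 1.9 | 4% to 6% |
| 11 v 14 | 0.87 to 0.96 | 0.7 to 1.6 | 3% to 5% |

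**With a fixed window from surgery.** The same window applies to both arms, so equal true risk gives equal expected counts: 20% v 20% over the full period in this illustration, risk ratio 1.00.

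**The case against.** The strongest objection is that the bias is conditional. The protocol does not predict a difference in stay for this trial; it measures stay as an outcome. The 3-day figure comes from one small study whose validity the protocol itself questions. This stands: a reader might infer from the Background that the complication comparison is bound to be biased, but the document supports only a bias that appears if stays differ.

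A reader might also infer a larger effect by letting events arise at a constant rate throughout the stay. Recorded events would then be in the ratio (L − 3)/L: 4/7 = 57%, 7/10 = 70% or 9/12 = 75% for standard-arm stays of 7, 10 or 12 days. Those ratios cover only complications without readmission, and they rest on assumed stays and an assumed constant rate. Crediting readmitted events weakens them. With a 20% risk spread evenly over 14 days and stays of 10 and 7 days, 14.3% v 10.0% becomes 14.9% v 11.0% (ratio 0.74) if 10% of later events are readmitted, or 16.0% v 13.0% (0.81) if 30% are. Onset concentrated early, with the longer stays assumed, brings the ratio closer to 1.

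The illustration also treats stay as unrelated to complications. A patient with a wound problem may be kept in longer, so part of any difference in mean stay could be a result of complications. The difference in time at risk would then be less than the difference in mean stay. This too stands as a limit on the size.

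The definition has merits: events in the records are documented, and in-hospital and readmission events are those that enter the inpatient cost outcome. That is a reason to keep them as a breakdown, but it does not give the arms equal observation. Finally, the case report form is a separate booklet that is not shown, so complications may also be noted at visits. Even so, the outcome as defined would leave out a post-discharge event without readmission.

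**Conclusion.** The point holds as a conditional one. The stated definition makes the observation window for complications without readmission equal to the length of stay, which the approach may alter. Neither the visit schedule nor the planned test corrects for this. If stays differ, the recorded comparison leans towards the shorter-stay arm; if they do not, it is unbiased in this respect.

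Under the assumptions shown, with only the 3-day gap taken from the protocol, the distortion is modest: a recorded risk ratio of about 0.72 to 0.96 and a gap of 0.7 to 3.6 percentage points, with no true difference. The actual size cannot be fixed from the document. The point touches one secondary outcome. The Knee Society Score, the sample size and the interim rule on the primary endpoint are unaffected. It is worth changing because the change is cheap and because events that were never recorded cannot be recovered at analysis.

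**What to change.** In Secondary outcomes – medical records, define the complication comparison over fixed windows from the date of surgery, for example to 6 weeks and to 52 weeks, counting events wherever they are treated. In Assessments/data collection, add complications to what is recorded at the existing 1, 6, 12 and 52 week assessments. Report in-hospital events and those requiring readmission as a descriptive breakdown, which also continues to serve the cost outcome.

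The cost is about one item on the case report form at visits already planned, or none if the form already has it. The downside is some recall-based reporting of minor events, most of all over the long interval between 12 and 52 weeks, and a slightly higher reported complication rate in both arms.

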### Secondary outcomes – independently assessed by physiotherapist

1. Flexion/extension range of motion (degrees)

2. Time to straight leg raise (days)

### Secondary outcomes – health economic

1. Cost of inpatient care including operative/diagnostic, length of stay, length of operation staff costs, complications/re-admissions and consumables

## Assessments/data collection

All trial proformas will be supplied in a separate booklet and will form the basis of the patients case report form. Assessment will be conducted pre, peri and post-operatively. Data on the primary and all patient based and independently assessed secondary outcome measures will be collected at 1, 6, 12, and 52 weeks postoperatively. These assessments are timed to coincide with routine clinical practice.

## Statistical considerations

### Sample size

In a group of 86 patients undergoing total knee arthroplasty the mean 1 year post-operative Knee Society Score was 172.2 with a standard deviation of 20 and a range of 98–200 [14]. To detect a 5% increase in the post-operative Knee Society Score in the sub-vastus group compared to the medial parapatellar group with a two sided significance level of 5% and a power of 90% a sample size of 105 patients would be required in each group. An additional 10% will be recruited to each group to allow for any patients lost to follow-up, giving a total sample size of 231.

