## Trial summary

This study aims to compare the effectiveness and efficiency of a standard medial parapatellar approach versus a sub-vastus approach in total knee replacement and to evaluate the clinical outcomes of care in each group. We propose a randomised controlled trial, with follow-up at 52 weeks, in a large sample population of 230 patients with patient based outcomes. The trial summary can be seen in figure 1. Patients will be recruited at their pre-operative assessment with randomisation taking place on their day of admission for surgery. Clinical and functional assessments will be carried out by a research nurse and physiotherapist respectively, pre and post-operatively, with the physiotherapist unaware of the approach taken. The primary outcome measure for the study is the Knee Society Score [12] and this will be collected at baseline and at 1, 6, 12 and 52 weeks post-operatively. Other outcome measures will include patient based (EuroQol 5D [10], WOMAC Index [11]), clinical (complications, blood loss, use of analgesia) and functional (range of motion) measures. Data will be analysed on an intention to treat basis with the principal comparisons being the mean difference in the Knee Society Score between the two groups at 1, 6, 12 and 52 weeks post-operatively.

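### For a 5% gain on a mean of 172.2 with SD 20, 90% power needs 114 to 115 patients per group; the stated 105 gives about 87%

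*Protocol article*

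**What the plan says.** The Sample size section of the protocol article draws on a cited series of 86 patients, in whom "the mean 1 year post-operative Knee Society Score was 172.2 with a standard deviation of 20". The target is set as a percentage: "To detect a 5% increase in the post-operative Knee Society Score in the sub-vastus group", relative to the medial parapatellar group, with a two-sided 5% test. The result is "a power of 90% a sample size of 105 patients would be required in each group". An allowance for loss follows: "An additional 10% will be recruited to each group to allow for any patients lost to follow-up, giving a total sample size of 231".

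The endpoint being sized matches the Assessment of outcome section: "The primary outcome measure for this study will be the Knee Society Score [12] at 52 weeks".

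The Sample size section does not give the target difference in points and mentions no rounding. It claims no reduction in sample size from baseline adjustment or repeated measurements.

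**The concern.** Every input to a two-group comparison of means is printed, so a reader can redo the calculation, and the result is not 105. This is the article's only statement of power for the primary endpoint. If the 52-week comparison shows no difference, readers will take it that a true 5% gain had a 10% chance of being missed. On the printed inputs that chance is somewhat larger, and the difference detectable with 90% power is somewhat larger than 5%.

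**Working it through.** **Inputs (all from the Sample size section).** Mean 172.2; SD 20; increase 5%; two-sided significance 5% (z = 1.960); power 90% (z = 1.2816); equal groups.

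**Difference in points.** 0.05 × 172.2 = 8.61, a standardised difference of 8.61/20 = 0.4305.

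**Trying to reproduce 105.** The formula per group is n = 2 × (1.960 + 1.2816)² × SD² / difference².

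- Normal approximation: 2 × 10.507 × 400 / 74.13 = 113.4, so 114 per group.
- Two-sample t-test (noncentral t): 114.4, so 115 per group.

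The stated 105 is 9 to 10 per group below this.

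**Power of 105 per group for 8.61 points.**

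- Standard error of the difference: 20 × √(2/105) = 2.760.
- Normal approximation: 8.61/2.760 = 3.119, and 3.119 − 1.960 = 1.159, which gives 87.7%.
- t-test: 87.4%, so the type II error is 100 − 87.4 = 12.6%.

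**Other readings, normal approximation, per group.**

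| Reading | n per group |
|---|---|
| One-sided 5%, 90% power, 8.61 points | 93 |
| Two-sided, 85% power, 8.61 points | 97 |
| Two-sided, 80% power, 8.61 points | 85 |
| 5% of 200 (top of the quoted range) = 10 points, 90% power | 85 |
| Ratio of 1.05 on the log scale, 90% power | 119 |
| 8.61 points with a Wilcoxon efficiency correction | 119 or more |
| 9 points, two-sided, 90% power | 104 (t-test 104.7, so 105) |

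Of these, a 9-point difference is the one that returns the stated number: 2 × 10.507 × 400 / 81 = 103.8 by the normal approximation and 104.7 by the t-test. With 105 per group, the t-test power for 9 points is 90.1%. Nine points is 9/172.2 = 5.2% of the stated mean.

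**The case against.** The strongest reply is that 5% is a rounded description of a target set in whole points. Nine points is 5.2% of 172.2, which is 5% to the nearest whole percent, and a t-test for 9 points needs exactly 105. On that reading the calculation is sound and only the absolute difference is missing. This is plausible, and it is why the matter is one of reporting. It remains an inference, because the text gives a percentage and a mean but no difference in points. Nor can a percentage rounded that coarsely fix the sample size. Anything from 4.5% (7.749 points; 8,406/60.05 = 140 per group) to 5.5% (9.471 points; 8,406/89.70 = 93.7, so 94) would be printed as 5%, where 8,406 = 2 × 10.507 × 400.

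A second reply is that 231 recruits are about 115 per group, which gives about 90% power for 8.61 points. That holds only if nobody is lost, and the article reserves the extra patients for loss to follow-up.

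A third is that the Data analysis section plans repeated measures analysis of variance, which could be more efficient than a single unadjusted comparison. It could, and so the 87% belongs to the simple two-group comparison that the Sample size section describes. No correlation between baseline and 52 weeks is given. If baseline were adjusted for, assumed correlations of 0.1, 0.3 and 0.5 would give power of about 87.4–87.7%, 90.0–90.2% and 94.6–94.8% with 104 to 105 per group. The stated 90% cannot be rested on an unstated value from that range.

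**Conclusion.** The sentence is wrong on its own inputs. For 8.61 points, 90% power needs 114 to 115 per group, and 105 gives about 87%. The shortfall is under 3 percentage points of power. This assumes that the 5% is taken of the quoted mean of 172.2 and that the groups are compared without adjustment, as the Sample size section implies.

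A reader might infer more, and the documents do not support it:

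- **That the trial is materially underpowered.** The same 105 per group has 90% power for 9 points, only 0.39 points more than 8.61, and the final analysis may be more efficient than the sizing assumed.
- **That the allowance for loss is miscalculated.** The article says that 10% is added to each group, and 210 × 1.10 = 231. It does not state a 10% loss rate that would call for division by 0.9.
- **That the 230 patients in the Trial summary point to a second design.** A difference of one patient from 231 is clerical and has no statistical consequence.

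**What to change.** Restate the sentence in the Sample size section, in whichever form matches the calculation actually made:

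- *105 patients per group give 90% power, at a two-sided 5% level, to detect a 9-point (5.2%) difference in Knee Society Score, assuming an SD of 20*; or
- *105 patients per group give about 87% power, at a two-sided 5% level, to detect a 5% (8.61-point) difference, assuming an SD of 20*.

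Either form puts the difference in points on record, so that the calculation can be repeated and a null result read against the right figure. The number recruited stays as it is. The cost is one sentence and a slightly less favourable stated figure: a slightly larger detectable difference, or slightly lower power.

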### Data analysis

Intention to treat analysis – all patients entered into the trial will be followed up in the group to which they were randomly allocated regardless of which treatment they received. Continuous data will be analysed using repeated measures analysis of variance while the chi square test will be used to compare all categorical data. Baseline characteristics of the group will be compared using appropriate parametric and non parametric tests to ensure balance has been achieved with randomisation.

The principal comparisons will be between:

a) Comparison of the mean total Knee Society Score between the two groups at 1, 6, 12 and 52 weeks post-operatively.

b) Comparison of all secondary outcome measures between the two groups.

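### Repeated measures ANOVA is fixed for all continuous outcomes, although five are single measurements and two are times to an event that can be censored (minor; secondary outcomes only)

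*Protocol article*

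**What the plan says.** The Data analysis section assigns methods by data type alone: "Continuous data will be analysed using repeated measures analysis of variance while the chi square test will be used to compare all categorical data". It states no exception. The freedom to choose between parametric and non-parametric tests appears only in the next sentence, which concerns baseline characteristics. The same section lists among its principal comparisons "Comparison of all secondary outcome measures between the two groups", so the rule governs the secondary outcomes too.

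Those outcomes are of three kinds:

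- **Repeated scores and measurements.** The Assessments/data collection section has the primary, patient-based and physiotherapist-assessed outcomes collected at 1, 6, 12 and 52 weeks. These include the Knee Society Score, WOMAC, EuroQol, SF-36 and range of motion.
- **Single values.** The medical-records list has length of stay, tourniquet time, blood loss and the surgeon's ease-of-exposure score. The health economic list has the cost of inpatient care. Neither list is in the 1, 6, 12 and 52 week schedule.
- **Times to an event.** The physiotherapist-assessed list has "Time to straight leg raise (days") and the patient-based list has "Time to normal activities/return to function (days/weeks"). Both lists fall under the visit schedule, but asking at several visits when an event happened still gives one event time per patient.

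**The concern.** The stated method needs several measurements per patient. Five secondary outcomes have one, so the protocol names a model that has to be replaced before it can be fitted. Two more are times to an event. For these, a patient may leave the study or reach the last contact without the event, and all that is known is that the time exceeds the time observed. ANOVA has no place for such an observation.

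These outcomes are close to the reason for doing the trial. The Background reports that an earlier study found straight leg raise 4 days sooner and a hospital stay 3 days shorter with the sub-vastus approach. The Discussion names quicker rehabilitation and shorter stay as what surgeons are under pressure to achieve. If the stated method does not fit, the actual one has to be chosen later, possibly with the data in view. For the two times to event, a literal use of the rule could also distort the comparison.

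**Working it through.** **1. Single-value outcomes.** With group g, patient i and occasion k, a repeated measures ANOVA is

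y(gik) = mean + group(g) + patient(i within g) + occasion(k) + group × occasion(gk) + error(gik).

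With one occasion, the occasion and interaction terms vanish, and the patient term cannot be separated from the error. What remains is

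y(gi) = mean + group(g) + error(gi),

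which is a one-way ANOVA. For two groups, F = t², the ordinary two-sample t-test. So a valid comparison of means is available, but it is not the stated method. It also ignores surgeon and gender, the two minimisation variables in the Randomisation section.

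**2. Does the plan itself expect patients without complete follow-up?** The Sample size section gives 105 per group and adds 10% for loss:

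- 2 × 105 × 1.10 = 231, which reproduces the stated total.
- 231 − 210 = 21 patients allowed for loss, and 21/231 = 9.1% of those recruited.

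This is a planning allowance for loss to follow-up. It does not give the number censored on either time outcome. A patient who reached the event before being lost is fully observed. A patient still in follow-up who has not returned to normal activities is censored without being lost.

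**3. What omission does to a time to event.** In group g, let p(g) be the proportion with no observed event time, m(g) the mean time among those observed, and s(g) the mean that the others would have had. Then

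- true mean = (1 − p(g)) × m(g) + p(g) × s(g)
- understatement when the others are omitted = true mean − m(g) = p(g) × (s(g) − m(g)).

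Unobserved times are those that outlast the observation, so s(g) normally exceeds m(g) and both groups look faster than they are. The error in the between-group difference is the difference of the two understatements. If the gap s − m is the same value D in both groups, it is (p(1) − p(2)) × D. It vanishes when the proportions are equal; otherwise it flatters the group with more non-recoverers.

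The document gives neither p(g) nor D for either outcome, so no figure can be attached. Only the direction follows.

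**4. How likely is censoring?** For straight leg raise, the unit is days, the difference reported in the Background is 4 days, and follow-up runs to 52 weeks. Little censoring is plausible, though the document gives no proportion. Return to normal activities is recorded in days or weeks and depends on the patient's own recovery, so censoring is easier to envisage. Again no proportion is given.

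**The case against.** The strongest reply is that this is a condensed article. The choice of test for each secondary outcome is commonly left to the full protocol or analysis plan, and a sensible reader would apply repeated measures ANOVA only where measures repeat. That would carry weight if the article were silent. It is not: it states one method for continuous data and gives latitude only for baseline comparisons. The point is therefore a rule that does not fit the listed outcomes, not a missing detail.

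Three other replies stand, in whole or in part:

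- **Single values can be analysed.** A reader might infer that the five single-value outcomes have no valid analysis. The reduction to a t-test shows otherwise. For these, the defect is loose wording and the lack of adjustment, and no biased result has been shown.
- **The censoring harm is conditional.** The article does not say that patients without an event time will be dropped, and the size of any bias is unknown. What stands is that ANOVA leaves only omission or an assigned value, and no method that handles censoring is named for either outcome.
- **The chi-square half of the rule is not shown to fail.** A reader might infer that it breaks down for rare complications. The article gives no expected complication rate for the trial. Its only rates are the 17%, 21% and 10% cited in the Background for patellar complications. With about 115 per group (231/2 = 115.5), these give 115 × 0.10 = 11.5 to 115 × 0.21 = 24.15 expected events per group. The exact size of the uncorrected test, found by enumerating two binomials, is then 5.0% to 5.2% against a nominal 5%. At assumed rates of 1%, 2% and 3% it is 1.8%, 4.3% and 4.4%, which is conservative and not inflated. The documents do not support a finding there.

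**Conclusion.** The point holds as a minor one. The rule misfits seven secondary outcomes to different degrees. For length of stay, tourniquet time, blood loss, ease of exposure and inpatient cost, it collapses to an unadjusted comparison of two means. For time to straight leg raise and time to normal activities, it has no valid way to use patients without an observed event, and omitting them favours the group with more of them.

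The direction of that bias rests on two assumptions: unobserved times are longer on average than observed ones, and the gap is similar in the two groups. Its size cannot be computed from the document and may be small for straight leg raise.

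It would be wrong to infer that the main result is at risk. The primary Knee Society Score is truly repeated, the rule fits it, and its analysis is unaffected.

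**What to change.** Replace the sentence on continuous data with three:

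1. Repeated measures analysis is used only for outcomes actually measured repeatedly at 1, 6, 12 and 52 weeks.
2. Continuous outcomes with one value per patient (length of stay, tourniquet time, blood loss, ease of exposure, inpatient cost) are compared with a linear model adjusted for surgeon and gender, the minimisation factors.
3. Time to straight leg raise and time to normal activities are described with Kaplan-Meier curves and compared by log-rank test or Cox model. Patients without the event are censored at last contact.

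The third line keeps every randomised patient with any follow-up in the comparison, in keeping with the intention-to-treat statement. It assumes that loss is unrelated to recovery within each group, which should be said when results are reported.

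The cost is analysis wording. It needs no new data, provided that the date of last contact is recorded for each patient. The change should be made before any unblinded comparison of these outcomes.

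### The primary outcome and sample size concern the 52-week Knee Society Score, but the analysis is a repeated measures ANOVA over four unranked visits with no 52-week contrast named as the primary test

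*Protocol article*

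**What the plan says.** The Assessment of outcome section fixes one time point: "The primary outcome measure for this study will be the Knee Society Score [12] at 52 weeks".

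The Sample size section uses the same time point. It cites a series in which "the mean 1 year post-operative Knee Society Score was 172.2 with a standard deviation of 20 and a range of 98–200", and plans "To detect a 5% increase in the post-operative Knee Society Score in the sub-vastus group" over the standard approach. The error rates and the resulting size are given as "two sided significance level of 5% and a power of 90% a sample size of 105 patients would be required in each group". A further 10% for loss to follow-up brings the total to 231.

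The Data analysis section gives one method for every continuous outcome: "Continuous data will be analysed using repeated measures analysis of variance". Item (a) of its principal comparisons is the group comparison of mean total Knee Society Score at weeks 1, 6, 12 and 52, and the Trial summary says the same. Neither place sets week 52 apart or says which ANOVA term decides the trial. On the analysis population, the section says that "all patients entered into the trial will be followed up in the group to which they were randomly allocated". It gives no rule for patients who miss a visit.

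**The concern.** A repeated measures ANOVA with two groups and several visits conventionally reports two tests that involve treatment. The group main effect compares the arms on the average over visits. The group-by-time interaction asks whether the difference between arms varies across visits. Neither is the difference at week 52, which is the quantity that the trial names as primary and is powered on.

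This matters here because the article's own Background describes a benefit that may fade: a quadriceps strength advantage of 35% at 1 week and 16% at 1 month. It says that long-term follow-up is needed to learn whether short-term gains last. A test that pools the visits can be positive when nothing remains at 52 weeks, and can be weak when the difference is present only then. With no term designated in advance, the choice of which result answers the primary question is left until the data are in.

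**Working it through.** **1. The plan's own sample size.** Inputs from the Sample size section: mean 172.2, SD 20, 5% increase, two-sided 5%, power 90%.

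- Difference: 0.05 × 172.2 = 8.61 points.
- n per arm = 2 × 20² × (1.960 + 1.282)² / 8.61² = 113.4, so 114. The stated 105 is not reproduced. A difference rounded to 9 points gives 103.8, so 104 (105 with the t distribution), which is probably its source.
- Total: 210 × 1.1 = 231, as stated.

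This gap does not affect the point below. What matters is that the calculation is for a single two-group comparison at one year.

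**2. Assumptions for the ANOVA.** The article gives no visit-specific SDs or correlations. I assume SD 20 at each of the four post-operative visits, the same correlation ρ between any two visits (0.3, 0.5 or 0.7), and n = 231 × 0.9 / 2 ≈ 104 per arm.

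**3. Formulas.**

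- Direct 52-week test: noncentrality λ = (n/2) × 8.61² / 400 = 9.64 on F(1, 206). Power is 87%.
- Group main effect: the variance of a patient's four-visit mean is V = 400(1 + 3ρ)/4, which is 190, 250 or 310. λ = (n/2) × (mean effect)² / V on F(1, 206).
- Group-by-time: λ = (n/2) × (sum of squared deviations of the visit effects from their mean) / [400(1 − ρ)] on F(3, 618). With the effect at one visit only, or at three of the four, that sum is 0.75 × 8.61² = 55.6.

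**4. Results.**

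| True effect | Mean effect (points) | Test | ρ = 0.3 | ρ = 0.5 | ρ = 0.7 |
|---|---|---|---|---|---|
| 8.61 at week 52 only | 8.61/4 = 2.15 | Group main effect | 20% | 16% | 14% |
| 8.61 at week 52 only | – | Group-by-time | 77% | 90% | 99% |
| 8.61 at weeks 1, 6, 12; zero at 52 | 3 × 8.61/4 = 6.46 | Group main effect | 92% | 83% | 75% |
| 8.61 at weeks 1, 6, 12; zero at 52 | – | Group-by-time | 77% | 90% | 99% |
| 8.61 at all four visits | 8.61 | Group main effect | 99% | 97% | 94% |

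The interaction has identical power for an effect confined to week 52 and for one absent only at week 52. It can say that the visits differ, but not which of them carries the effect.

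**5. Incomplete patients, conditional on implementation.** If the ANOVA were run on complete cases, with 10% lost by week 52 and an assumed independent 3% or 5% missing at each earlier visit, the complete cases would be 231 × 0.9 × 0.97³ ≈ 190 or 231 × 0.9 × 0.95³ ≈ 178. About 231 × 0.9 ≈ 208 would have a 52-week score.

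**The case against.** The strongest reply is that the 52-week comparison is already in the plan. Item (a) of the principal comparisons and the Trial summary both name it, and visit-specific contrasts are often taken from a repeated measures analysis. That stands: the comparison is not omitted, and no sentence says that the main effect is the headline result. But it is one of four comparisons of equal rank, and nothing ties it to the ANOVA as the deciding test. Reading item (a) as four separate 5% tests does not help. The chance of at least one false positive is then 1 − 0.95⁴ = 18.5% if the visits are independent, and 13-17% by simulation at correlations of 0.7 to 0.3.

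Second, the low main-effect power is only part of the picture. Group-by-time would usually flag a late-only effect, and for a sustained effect the main effect does better than a single 52-week test (94-99% against about 87%). Both are true. So the ANOVA as a whole would not necessarily overlook a late effect; the weakness for such an effect lies in the main effect.

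Third, the trial's hypothesis covers short-term as well as long-term function, so detecting an early effect is not an error in itself. That also stands. The difficulty is that an early effect could be reported as the primary result when the declared primary time point shows none.

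A reader might also infer that the plan discards every patient with a missed visit and so breaks its intention-to-treat promise. The article does not support that. Complete-case deletion is conventional behaviour of classical repeated measures ANOVA, but it depends on the software and the model fitted. The handling of missing visits may properly sit in an analysis plan not shown, and the intention-to-treat statement concerns allocation, not missing scores.

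**Conclusion.** The point holds as a mismatch between endpoint and analysis. The primary outcome and the power calculation are for week 52. The prescribed method and the list of principal comparisons treat four visits alike and designate no 52-week contrast as the primary test. The 90% power figure therefore does not describe the standard ANOVA tests.

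The consequence depends on the shape of the effect. It is serious for the main effect if the effect is confined to week 52 or has vanished by then, and favourable to the main effect if the effect is sustained. The percentages rest on equal SDs of 20, a common correlation of 0.3 to 0.7 and 104 per arm, none of which the article gives for the repeated measures setting. The mismatch itself does not depend on them. The possible loss of patients with a 52-week score but a missed earlier visit is conditional on how the model is fitted and is a secondary matter.

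**What to change.** In the Data analysis section and the Trial summary, state that the single primary test is the between-group difference in Knee Society Score at 52 weeks, adjusted for baseline score and for the minimisation factors, surgeon and gender. Take it as the 52-week contrast from a mixed model with group, visit and group-by-visit terms, fitted to all available post-operative scores. A 52-week ANCOVA would also serve. Name the contrasts at weeks 1, 6 and 12 as secondary.

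The mixed model has the further merit that a patient who misses an earlier visit still contributes the 52-week score. The change is to analysis wording only: it needs no new data, visits or patients, and it brings the test into line with the endpoint on which the trial was sized.
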